## Introduction

### Head and neck cancer and its associated psychological issues

Head and neck cancer is a group of biologically similar cancers that affect the oral cavity, lips, nasal cavity, paranasal sinuses, pharynx, and larynx. It affects 550,000 people worldwide annually, leading to 300,000 deaths each year [1]. In Malaysia, 9,419 head and neck cancer cases were reported between 2007 and 2011, accounting for 9.1% of all cancer diagnoses [2]. Therefore, head and neck cancer is the country’s fourth-most-prevalent cancer [2]. Head and neck cancer leads to high incidence of various psychosocial issues among cancer survivors, such as depression, suicide, interpersonal relationship conflict, facial disfigurement, damage to self-image, social isolation, and continued substance dependence and abuse [3]. These psychosocial issues may lead to negative consequences in head and neck cancer survivors. For example facial disfigurement can increase depression and reduce quality of life (QoL) among head and neck cancer patients [4].

Some studies have found that head and neck cancer is associated with the highest documented rates of depression and anxiety compared with other cancer types [5]. Depression and anxiety could reduce head and neck cancer patients’ QoL [6]. A 2003 article by Spiegel and Giese-Davis pointed out that depression may predict cancer’s progression and mortality through a bidirectional relationship between depression and cancer; depression and cancer can negatively affect each other [7]. Consequently, depression and anxiety among head and neck cancer patients should be adequately treated.

*Experiential avoidance* (EA) has been broadly defined as attempts to avoid thoughts, feelings, memories, physical sensations, and other internal experiences—even when such avoidance causes long-term harm [8]. Currently, negative thoughts, emotions, and sensations are believed not to contribute to psychiatric illnesses; however, a habitual and persistent unwillingness to experience uncomfortable thoughts and feelings (and the associated avoidance and inhibition of these experiences) is thought to be linked to psychiatric illnesses [8, 9]. Additionally, reduced EA also indirectly predicts a higher QoL among cancer patients via its effect on depression symptoms [10]. Therefore, an intervention that successfully reduces EA is predicted to also reduce depression and anxiety symptoms.

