All participants will be permitted to withdraw from the study at any time without specifying the reason for their withdrawal, and we will not use any of the information collected from participants who choose to withdraw. Prior to their participation in this study, participants will be informed that the results of this study will only be used for research purposes and will not be recorded in patients’ case files. Participants’ personally identifiable information will not be sought or recorded, and participants’ anonymity will be assured. Each participant will be sequentially assigned a research number (e.g., *RCT001*, *RCT002*, etc.). All documents involved in this study’s assessment of research subjects—including participants’ personal information (socio-demographic, substance history, symptomatology, and questionnaire responses)—will be stored in document files and locked in a cabinet whose key is kept by the corresponding author.

Participants may also withdraw from the study if an adverse event occurs. An *adverse event* (AE) is any untoward medical occurrence involving a participant in a trial intervention that does not necessarily causally relate to this treatment. An AE can be any unfavorable or unintended sign, symptom, or disease that is temporarily associated with the use of an investigational intervention, whether related or unrelated to the investigational intervention. Participants will be issued a study card featuring the research team’s contact details and encouraged to maintain close contact by phone and report any AE. If an AE occurs, the event will be reported in the “Adverse Event” section of the study’s case report form (CRF), and a serious adverse event report will be filled out if necessary (S1 Fig). Such reports would include the AE’s name, date of onset and date of recovery, severity, relationship to the studied intervention, measures undertaken regarding the studied intervention, treatment, and outcome (whether resolved or ongoing). All serious AEs will be reported to the Human Research Ethics Committee of Universiti Sains Malaysia. AE-related criteria that would exclude participants from the study are:

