The presence of adverse reactions unrelated to the study that cause subjects to feel uncomfortable continuing this studyThe presence of adverse reactions that may be related to the study, such as an unusual illness that started after a studied interventionUnusual changes in participants’ behavior, temperament, routine, suicidal tendency, or psychotic symptoms that began after a studied interventionAny suspected or unexpected adverse events inconsistent with the generally accepted administration of the ACT and MBSR; in general, psychotherapy patients should not exhibit any side effects or health-detrimental effects

If an unexpectedly serious AE is reported in a subject or more in any of the randomized intervention group (ACT or MBSR), an interim analysis will be conducted to investigate this matter. If the findings of this investigation indicate any safety concerns which is related to the intervention administered (ACT or MBSR), the Trial Monitoring Committee will terminate the trial prematurely. Serious AE which are indication for premature termination of trial include suicidal tendency, life-threatening self-harm, and hospitalization related to psychological adverse events arise from the intervention administered.

Only the study’s corresponding author and co-authors are permitted to access the study’s files for data analysis or publication purposes. The findings of this study will be submitted for publication in peer-reviewed academic journals and for presentation at international conferences and symposia. The study’s principal investigator will be listed as the corresponding author, and authorship eligibility will be based on the International Committee of Medical Journal Editors’ recommendations.

All of this study’s investigators declare no financial or other competing interests in conducting this study.

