### Inclusion criteria

The study’s inclusion criteria will include: (1) patients who have been newly diagnosed with head and neck cancer (within the previous month), whose diagnosis has been confirmed by a histopathological examination report, who have been treated only with surgery or have yet to received treatment, and who are at any cancer stage except metastasis to the central nervous system; (2) patients aged 18 years and older; (3) patients who have undergone surgery and plan to receive the standard regime of radiotherapy or chemotherapy; (4) patients who have developed depression and anxiety symptoms after their head and neck cancer diagnosis with a “Hospital Anxiety and Depression Scale” (HADS) depression subscale score of ≥ 8 and an anxiety subscale score of ≥ 8; and (5) patients who are able to read and understand written Malay.

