### Recruitment process

This study will use a consecutive sampling method. The research team will approach head and neck cancer patients registered at the two targeted institutions and explain the study’s objectives and procedures. Patients who are interested in participating in this study will be screened for inclusion and exclusion criteria by a research team member. All eligible patients will be invited to participate in this study. The study’s purposes and procedures will be thoroughly explained (verbal explanation by the research assistant and a copy of the participant information will also be distributed) to prospective participants before they are invited to participate in this study, their anonymity will be assured, and they will be informed of their right to withdraw from the study at any time and the data collected will be discarded. Eligible patients will be given 48 hours to decide on their participation in the study. Then, participants will sign written informed consent to participate in the study before they enroll in the study.

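### The rule that withdrawn participants' data are not used has no exception for adverse-event records, although an adverse event is a stated reason to withdraw and serious events drive the stopping decision

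*Protocol article*

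**What the plan says.** All of the following is in the Protocol article.

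- **Withdrawal, Support and ethics:** participants may leave at any time without giving a reason, and "we will not use any of the information collected from participants who choose to withdraw".
- **Withdrawal, Recruitment process:** before consent, "they will be informed of their right to withdraw from the study at any time and the data collected will be discarded".
- **AE as a ground for leaving, Support and ethics:** "Participants may also withdraw from the study if an adverse event occurs". A list of AE-related criteria for taking a participant out of the study follows; new suicidal tendency is among them.
- **AE reporting, Support and ethics:** participants receive a study card and are "encouraged to maintain close contact by phone and report any AE". An AE that occurs goes into the AE section of the case report form (CRF), and all serious AEs go to the ethics committee. Neither duty is limited to particular arms.
- **Stopping, Support and ethics:** an interim analysis follows if an unexpectedly serious AE "is reported in a subject or more in any of the randomized intervention group (ACT or MBSR"). If it finds a safety concern related to the intervention, the Trial Monitoring Committee ends the trial. "Serious AE which are indication for premature termination of trial include suicidal tendency, life-threatening self-harm", together with hospitalization for psychological AEs arising from the intervention.

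**The concern.** The withdrawal rule is written without limits and is part of what participants are told before they consent. The safety rule a few paragraphs later needs exactly the kind of record that the withdrawal rule removes. People who leave because something went wrong are the group in which AEs are most to be expected, so the lost records would not be a random share.

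The population makes this more than a formality. The Introduction says that head and neck cancer leads to "high incidence of various psychosocial issues among cancer survivors, such as depression, suicide". Inclusion criteria admit only "patients who have developed depression and anxiety symptoms after their head and neck cancer diagnosis", with a HADS score of at least 8 on both subscales. Termination requires a judgement that an event is related to ACT or MBSR. In people who are distressed at entry, that judgement needs a complete set of events from all arms, including the events of those who left.

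**Working it through.** The plan gives no figure on this point, so the check is mainly a reading of the rules together.

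**Step 1. Follow one participant through the text.**
1. A participant has an AE. It is entered in the CRF.
2. The participant chooses to withdraw because of it, as Support and ethics allows.
3. The no-use sentence now covers any information collected from that person. Recruitment process has promised that it is discarded.
4. No sentence exempts the AE entry. Taken literally, the event is absent from any later triggered review and from the reported safety results, in whichever arm it occurred.

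**Step 2. Who is covered.** The no-use sentence concerns those who choose to withdraw. A participant taken out under the AE-related criteria has arguably not chosen. The boundary is not sharp, however: one of those criteria is that an adverse reaction unrelated to the study makes the person uncomfortable about continuing, which is close to a choice to leave.

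**Step 3. A ceiling on size.** Inputs from Participants: 40 per arm, 30% anticipated dropout.
- ACT and MBSR: 2 × 40 = 80; 0.30 × 80 = 24.
- All three arms: 0.30 × 120 = 36.

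This assumes that every dropout is a voluntary withdrawal and that dropout is spread evenly. Other measures also counts death, illness and loss to follow-up among the reasons, so the true number is lower. The number who withdraw because of an AE is lower still and cannot be derived from the document.

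**Step 4. Why control-arm events belong in the review.** Suppose therapy does no harm and each participant has an assumed background risk p of a qualifying event, independently. The chance of at least one event among n participants is 1 − (1 − p)^n.

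| Assumed p | ACT + MBSR, n = 80 | Control, n = 40 |
|---|---|---|
| 0.5% | 33% | 18% |
| 1% | 55% | 33% |
| 2% | 80% | 55% |
| 5% | 98% | 87% |

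For example, at 1%: 1 − 0.99^80 = 0.55. The document gives no value of p, so this is illustration only. It shows that a single event in the active arms can be quite likely without any effect of therapy, so the control count is needed to interpret it. A control-arm record discarded at withdrawal would weaken that comparison too.

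**The case against.** The strongest reply is that the withdrawal sentence was never meant to reach safety records. It stands among statements on research use and confidentiality, and the AE duties follow in their own paragraph. A serious AE reported before withdrawal has already led to a CRF entry and a report to the ethics committee and, if unexpected and in ACT or MBSR, to the review; nothing says these steps are reversed. Someone removed for new suicidal tendency may fall outside the rule altogether. All this narrows the effect. It does not supply the missing exception, and the promise made before consent is unqualified.

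A reader might infer more from the same text, and three stronger readings are not supported.

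- **That the trial would learn of suicidal events only if participants phone in.** Phone contact is the only route described as AE reporting. But the removal criteria on changed behaviour and suicidal tendency suggest that staff are expected to notice such changes, all arms have weekly sessions, and reasons for absence and dropout are recorded. The CRF form and the session appendix are not shown and may contain direct questions. A condensed article may leave this out.
- **That control-arm events are not collected.** CRF recording and reporting of serious AEs carry no arm restriction, and a trigger confined to ACT and MBSR is reasonable as a trigger. What is unstated is only that the review looks at the control events.
- **That the chance of missing a trigger can be quantified.** If only half of events were reported, the chance of at least one report among 80 would fall from 80% to 55% at an assumed 2% risk. Nothing in the document supports either input.

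**Conclusion.** The point holds as a defect in stated wording. Two sections tell participants and staff that withdrawn participants' information is not used, neither excepts AE records, and the same plan names an AE as a reason to withdraw and rests a stopping decision on such events. If the rule is followed as written, the safety review and the safety results can lose the events of people who left because of them.

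The size is unknown. The figures of 24 of 80 and 36 of 120 are loose ceilings that treat all anticipated dropout as voluntary withdrawal. The conclusion assumes a literal reading and that no document outside the article contradicts it. The missing statement about control-arm events is a smaller matter, worth settling in the same edit. Passive AE detection is not established as a defect.

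**What to change.** - **Support and ethics, Recruitment process and the consent information:** state that AE and serious AE records collected up to withdrawal are kept and used for safety review and safety reporting, whatever is done with the other data.
- **Support and ethics, interim analysis:** state that the triggered review sets ACT and MBSR events beside the control-arm events already recorded. The trigger itself can stay as it is.
- **Optional:** ask the same brief AE question in all three arms at t1 and t2. If the CRF already does this, a sentence saying so is enough.

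The cost is a few changed sentences, notified to the ethics committee in writing as the protocol already requires for modifications. The downside is that participants who withdraw can no longer have their safety records discarded, so they must be told this before they consent. For anyone who has already consented under the present promise, the ethics committee should decide how the change applies.

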### Participants

This study’s participants will be recruited from the source population. This population includes all newly diagnosed head and neck cancer patients who have been treated only with surgery or who have not yet received treatment and who are registered under the oncology and otorhinolaryngology unit of the Advanced Medical and Dental Institute (AMDI) at the Universiti Sains Malaysia (USM) or the oncology and otorhinolaryngology unit of Universiti Kebangsaan Malaysia Medical Centre (UKMMC). The study’s sample size was determined based on G-Power 3.1.9.2 for analysis of variance (ANOVA). This sample size was calculated based on continuous responses to the posttraumatic growth inventory used in the study by Labelle et al. (2015) [48] with a medium effect size (0.15) and a two-tailed alpha of 0.05. The results of this calculation indicated that the current study requires a total sample of 93 for three equal-sized groups to achieve a power of 0.8. Anticipating a drop-out rate of 30%, we estimated a total sample size of 120 respondents and 40 respondents for each group.

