MBSR is an eight-week, standardized group intervention comprising mindfulness meditation and gentle yoga designed to address stress, pain, and illness [40]. Cancer patients’ participation in MBSR has been shown to have increase in spirituality, PTG, self-compassion, and positive states of mind [41–47]. Studies have emphasized that MBSR increases PTG among participating cancer patients immediately after an eight-week intervention [44, 47, 48]. A meta-analysis of 29 studies with a total of 3,476 cancer survivors evaluated mindfulness-based interventions’ efficacy in facilitating mental well-being, revealing that MBSR significantly reduced depression, anxiety, stress, and fatigue while enhancing PTG, QoL, and mindfulness among cancer patients [49]. Moreover, MBSR has been reported to lower psychological distress and improve total, social, and emotional QoL among head and neck cancer patients [50]. To date, however, MBSR’s effect on cancer patients’ hope has not been investigated. Therefore, an investigation of MBSR’s effects on PTG, hope, optimism, depression, anxiety, and QoL among head and neck cancer patients would be interesting. Moreover, a comparison of MBSR’s efficacy compared to ACT would be valuable.

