#### Rationale

Head and neck cancer differs from other cancer types due to various psychosocial issues associated with it [3, 4]. Moreover, the devastating complications of both cancer itself and cancer treatments’ side effects—such as fatigue, pain, speech and swallowing problems, breathing problems, mucositis, xerostomia, and trismus—further disrupt many functions and daily living activities, increasing psychological distress and decreasing QoL [32, 33]. Therefore, an investigation of the psychosocial interventions that could enhance PTG, hope, optimism, and QoL among head and neck cancer patients is crucial. Reducing these patients’ internalized stigma and EA could also ultimately restore these cancer survivors’ mental and physical well-being. ACT and MBSR have been reported to enhance positive psychology and alleviate psychological distress among cancer patients [38, 49]. However, data regarding ACT and MBSR’s effects on positive psychology, psychological sequelae and QoL in head and neck cancer patients are lacking. ACT’s effects on PTG, hope, optimism, QoL, depression, anxiety, and EA among head and neck cancer patients have not been studied. Although MBSR has been reported to lower psychological distress and enhance QoL in head and neck cancer patients, its effects on positive psychology and EA have not been investigated. Hence, MBSR may act as a good comparator intervention to ACT for evaluating its efficacy on positive psychology, psychological sequelae and QoL among head and neck cancer patients. Therefore, we have proposed a three-armed RCT to evaluate these effects over time compared to a control group receiving treatment-as-usual.

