### Objectives

#### Primary objectives

Evaluate ACT’s efficacy in enhancing PTG among head and neck cancer patients compared to MBSR and a control (treatment-as-usual) immediately after the eight-week intervention and 24 weeks post-intervention compared to pre-intervention

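### The stated 0.8 power belongs to the overall three-group test; for ACT versus MBSR, part of the primary objective, power is about 0.33–0.41 if MBSR gives half of ACT's benefit

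*Protocol article*

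**What the plan says.** The single primary objective (Protocol article, Primary objectives) concerns ACT's "efficacy in enhancing PTG among head and neck cancer patients compared to MBSR and a control (treatment-as-usual"), with MBSR named first. The Rationale adds that "MBSR may act as a good comparator intervention to ACT for evaluating its efficacy".

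The sample size (Participants) was obtained from "G-Power 3.1.9.2 for analysis of variance (ANOVA") with an effect size of 0.15 and a two-tailed alpha of 0.05. It concludes that the study "requires a total sample of 93 for three equal-sized groups to achieve a power of 0.8", and 120 patients are to be enrolled to allow for 30% drop-out. The input comes from reference [48], which the Introduction lists among the studies showing that "MBSR increases PTG among participating cancer patients immediately after an eight-week intervention [44, 47, 48"]. No ACT–MBSR difference is assumed anywhere, and no power is given for that contrast.

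Data analysis plans a one-way ANOVA of the three groups at each visit with a false discovery rate adjustment. Its main mixed model names two comparisons only: ACT with control, and MBSR with control.

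**The concern.** A three-group effect can arise almost entirely from two active therapies differing from control. It then says little about the difference between the therapies. For a fixed overall effect, the closer MBSR comes to ACT, the smaller the difference left between them. The protocol's own literature review says that MBSR works on this outcome, so a sizeable MBSR effect is the expected situation.

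The head-to-head comparison is in the objective and in the trial's title. If its power is low, a non-significant result is likely even when a real difference exists. With 0.8 as the only power figure in the article, a reader could take such a result as evidence that the two therapies are equally good.

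**Working it through.** **Inputs from the protocol.** Three groups at 1:1:1, three visits, effect size 0.15, alpha 0.05, N = 93 (31 per arm), 120 enrolled, 30% drop-out.

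**Assumed here, because the protocol does not state it.** The ANOVA variant, a between-visit correlation of 0.5, sphericity, MBSR's benefit lying between control and ACT, and no multiplicity adjustment of the pairwise test.

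**Step 1: reproduce 93.** For a group-by-visit interaction, the noncentrality is λ = f²·N·m/(1 − ρ), with df (3 − 1)(3 − 1) = 4 and (N − 3)(3 − 1).
- N = 93: λ = 0.0225 × 93 × 3 / 0.5 = 12.555, df 4 and 180, power 0.81.
- N = 90: λ = 12.15, power 0.796.

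So 93 is the first total with equal arms that exceeds 0.8. The other variants tried do not give 93:
- one-way ANOVA at f = 0.15: 432
- one-way at f = 0.25: 159
- one-way with f² = 0.15: 69
- repeated-measures between-group test at f = 0.15: 291
- repeated-measures within-subject test at f = 0.15: 75

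**Step 2: split the overall effect.** Let the arm effects be control 0, MBSR r and ACT 1, where r is MBSR's share of ACT's benefit. The sum of squares about the mean is SS = (2/3)(1 − r + r²). With λ held at 12.555:
- ACT versus MBSR: λ·[(1 − r)²/2]/SS
- ACT versus control: λ·[1/2]/SS

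At r = 0.5, SS = 0.5. The ACT–MBSR noncentrality is 12.555 × 0.125 / 0.5 = 3.14, and the ACT–control value is 12.555.

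**Step 3: power with 93 analysed (62 in the pair).** The 2-df test is the two-arm group-by-visit interaction (df 2 and 120). The 1-df test is a single contrast that carries the whole effect (df 1 and 60).

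| MBSR share r | ACT–MBSR noncentrality | ACT–MBSR, 2-df | ACT–MBSR, 1-df | ACT–control, 2-df |
|---|---|---|---|---|
| 0 | 9.42 | 0.78 | – | 0.78 |
| 0.25 | 6.52 | 0.61 | 0.71 | 0.86 |
| 0.50 | 3.14 | 0.33 | 0.41 | 0.89 |
| 0.75 | 0.72 | 0.11 | 0.13 | 0.86 |
| 1 | 0 | alpha | alpha | 0.78 |

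Using residual degrees of freedom pooled over all three arms changes these by about 0.01 at most.

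**Step 4: vary the number analysed.**
- 84 completers (120 × 0.7), r = 0.5: λ = 11.34, ACT–MBSR noncentrality 2.835, power 0.30 (2-df) or 0.38 (1-df).
- All 120, r = 0.5: λ = 16.2, ACT–MBSR noncentrality 4.05, power 0.41 (2-df) or 0.51 (1-df).
- All 120, r = 0.25: ACT–MBSR noncentrality 16.2 × 0.28125 / 0.5417 = 8.41, power 0.73 (2-df) or 0.82 (1-df).

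**Step 5: cross-check without the repeated-measures form.** The one-way effect that gives power 0.8 at N = 93 is f = 0.327. At r = 0.5, a two-sample t test with 31 per arm then has power 0.34. The result does not depend on reading the ANOVA as an interaction.

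I give no between-arm differences in SD units. An interaction f also absorbs the pattern over visits, so means scaled to f = 0.15 are not differences at any visit.

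**The case against.** **No figure is wrong.** This stands. The 93 reproduces, and the text ties 0.8 to an ANOVA of three equal groups. A reader might infer that the protocol claims 0.8 for ACT versus MBSR, but no sentence says so. What remains is a mismatch between a stated objective and the only power offered for it.

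**A condensed article may leave power per contrast to another document.** This is fair for the detail. It does not cover the main model, which the article does specify and which leaves out a comparison named in the primary objective.

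**At equality, 0.05 is not low power.** This stands. When MBSR equals ACT there is nothing to detect and the rejection rate is alpha, which no sample size changes. A single range such as 0.05–0.33 would mix the type I error rate with power.

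**The result depends on choices the protocol does not make.** This stands in part. At r = 0.5, power runs from 0.30 to 0.51 across test form and number analysed. The protocol gives no size for MBSR relative to ACT. At r = 0.25 the comparison is more likely than not to be significant (0.61–0.71 with 93), and it can reach 0.8 with all 120 analysed and a 1-df test. A reader might infer that non-significance is expected whatever the truth; that does not follow.

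**The equal-efficacy misreading is conjecture.** No section plans an equivalence claim, so this stands as a description of the text. A sentence ruling it out is a precaution.

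**Conclusion.** The concern holds in a limited form. The stated 0.8 is power for the overall three-group test. ACT versus control has similar or higher power (0.78–0.89, 2-df, N = 93), so the trial is reasonably sized for that comparison on its own assumptions. ACT versus MBSR has less power unless MBSR does little or nothing: 0.61–0.71, 0.33–0.41 and 0.11–0.13 when MBSR achieves 25%, 50% and 75% of ACT's benefit, with 93 analysed. At 50%, no combination of test and sample examined exceeds 0.51.

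These values assume f = 0.15 for the interaction, correlation 0.5, sphericity, MBSR between control and ACT, and no multiplicity adjustment. Any such adjustment would lower them. ACT–MBSR power of about 0.78 (2-df) needs MBSR to be no better than control, which conflicts with the evidence the protocol cites. The main mixed model's omission of the ACT–MBSR contrast adds to the problem: as written, the primary objective is not fully answered by the main analysis.

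**What to change.** **Participants (sample size).** State that 0.8 is the power of the overall three-group test. Give the ACT versus MBSR power with its assumptions: about 0.61–0.71, 0.33–0.41 and 0.11–0.13 at 25%, 50% and 75% of ACT's benefit with 93 analysed, and 0.30–0.51 at 50% across 84 to 120 analysed.

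**Data analysis.** Add the ACT–MBSR contrast to the mixed model and report it as an estimate with a 95% confidence interval. State that a non-significant difference will not be read as equal efficacy.

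**Cost.** No patients are added. There is one more contrast, a less favourable stated power for the head-to-head comparison, and the written notice to the review board that Support and ethics requires for changes to the data analyses.

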### Randomization

This study will use stratified permuted block randomization, stratifying trial participants according to their age (*18 to 40 years old*, *41 to 60 years old*, and *over 60 years old*) and gender (*male* and *female*). Participants will be randomized into three groups: an ACT group, an MBSR group, and a control group of patients on treatment-as-usual for intervention. Using a 1:1:1 allocation ratio and block randomization, we will randomly assign participants to the three groups. An allocation sequence will be generated via computer-generated random numbers, which will be obtained by a research assistant who is not otherwise involved in this study. The allocation sequence will be concealed in an opaque, sequentially numbered envelope.

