### Interventions

An eight-week psychosocial intervention will be administered to participants in each intervention group (MBSR and ACT) while participants in the control group will receive treatment-as-usual. The study’s outcomes will be assessed at three times: pre-intervention (t_0_), immediately after the eight-week intervention (t_1_), and 24 weeks after the intervention (t_2_).

Both the ACT and MBSR interventions will comprise eight sessions delivered at a rate of one session per week. Each session will last for one hour. At AMDI, USM, and UKMMC, chemotherapy for head and neck cancer lasts for 8 weeks, delivered at a rate of one session per week. Similarly, radiotherapy for head and neck cancer lasts for eight weeks at these institutions. Therefore, this study’s ACT and MBSR sessions will align with participants’ chemotherapy or radiotherapy sessions to ensure that all participants attend their intervention sessions. ACT and MBSR will be provided in group settings with intervention groups of 10 participants each.

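### The target of 120 multiplies 93 by about 1.3 instead of dividing by 0.7, so the planned 30% drop-out leaves 84 completers, 9 short of the 93 required for 0.8 power

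*Protocol article*

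**What the plan says.** All figures are in the protocol article.

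- **Requirement (Participants).** The calculation was done in G*Power for an ANOVA, "with a medium effect size (0.15) and a two-tailed alpha of 0.05". The study "requires a total sample of 93 for three equal-sized groups to achieve a power of 0.8", which is 31 per group.
- **Inflation (Participants).** "Anticipating a drop-out rate of 30%, we estimated a total sample size of 120 respondents and 40 respondents for each group". The Abstract repeats the total of 120 at 1:1:1.
- **Withdrawal (Support and ethics).** On those who leave by choice: "we will not use any of the information collected from participants who choose to withdraw". The Recruitment process section likewise has participants told of their right to withdraw and that their data will be discarded.
- **Other losses (Other measures).** Reasons for drop-out and loss to follow-up are recorded. The examples include feeling unwell and death as well as loss of interest or dislike of the intervention.
- **Analysis (Data analysis).** The primary analysis follows intention to treat. The main model is a linear mixed model over three visits, and multiple imputation is planned when between 5% and 40% of data are missing and are assumed to be missing at random.

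**The concern.** Three numbers stand side by side: 93 needed, 30% expected to drop out, 120 enrolled. They do not fit together. A drop-out rate is a share of those enrolled, so the enrolled number must be the required number divided by the share retained. Multiplying by one plus the rate gives too few, and the gap widens as the rate rises.

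This is the article's only power statement, and it concerns the primary outcome. If drop-out runs as the investigators expect, a non-significant result would be judged against a nominal 80% power that their own assumptions do not support.

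**Working it through.** **Inputs from the article:** 93 required in total, power 0.8, drop-out 30%, 120 enrolled (40 per group), effect size 0.15, alpha 0.05, three groups at 1:1:1, three assessments.

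**Inputs assumed, because the article does not give them:** the type of ANOVA, the correlation between visits, and sphericity. The effect size is taken as Cohen's f.

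**1. Reproducing 93.** For a repeated-measures within-between interaction with k groups and m visits:

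- λ = f² · N · m / (1 − ρ)
- df₁ = (k − 1)(m − 1)
- df₂ = (N − k)(m − 1)

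With f = 0.15, k = m = 3 and ρ = 0.5:

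| N | λ | df | Power |
|---|---|---|---|
| 90 | 0.0225 × 90 × 3 / 0.5 = 12.15 | 4, 174 | 0.796 |
| 93 | 0.0225 × 93 × 3 / 0.5 = 12.56 | 4, 180 | 0.811 |

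So 93 is the smallest total in equal thirds that reaches 0.80 under this setting. The other variants tried at f = 0.15 give different totals: 432 for a one-way ANOVA, 291 for the repeated-measures between-groups test, 75 for the within test (the last two also at ρ = 0.5), and 111 for the interaction with two visits. The interaction is therefore the likely source of 93, but the article does not confirm it.

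**2. Reproducing 120.**

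- Multiplying: 93 × (1 + 0.30) = 120.9. The stated 120 is this figure rounded down.
- Dividing: 93 / (1 − 0.30) = 132.9, so 133, or 135 (45 per group) for equal thirds.
- Check: 133 × 0.7 = 93.1 and 135 × 0.7 = 94.5, both at or above 93.

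**3. What 120 leaves.**

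- Completers at 30% drop-out: 120 × 0.7 = 84, or 28 per arm.
- Shortfall: 93 − 84 = 9, which is 9 / 93 = about 10%.
- Largest drop-out that still leaves 93: 1 − 93 / 120 = 22.5%.

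**4. Power at 84 completers.**

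- Under the setting in step 1: λ = 0.0225 × 84 × 3 / 0.5 = 11.34, df 4 and 162, power 0.763.
- If power at 93 is set to exactly 0.80 and the effect size is solved for, power at 84 is 0.751 to 0.755 under each of the five ANOVA variants tried.

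Steps 2 and 3 use only the article's figures. Step 4 depends on the assumptions listed above.

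**The case against.** The strongest reply is that 84 counts completers, while the planned analysis is not restricted to completers. Only participants who choose to withdraw have their data discarded. Patients who die or are lost to follow-up are also drop-outs, nothing says their earlier scores are thrown away, and a mixed model uses incomplete records. The analysed number therefore lies between 84 and 120.

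This stands, and it limits the point. A reader might infer that 30% drop-out and 0.8 power cannot both hold at 120, or that partial data cannot make up any of the loss. The documents do not support either. Suppose some of the 36 drop-outs supply t0 and t1 but miss t2, under the setting of step 1:

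- If the effect is present at t1 and sustained, 9 such patients bring power back to about 0.80 and 18 to about 0.83.
- If the effect grows in proportion to time up to a t2 at week 32 (24 weeks after an eight-week programme), all 36 bring it only to about 0.79.
- If the effect appears only at t2, little is recovered.

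The article gives neither the split of drop-outs by reason nor an expected effect pattern, so recovery is possible but cannot be counted on. The sample-size statement itself treats the 30% as lost, since it inflates for them.

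A second reply is that 30% might mean 30% of the 93, about 28 extra patients, which gives roughly 120. The text speaks of a drop-out rate and does not say this. Of 121 enrolled, 28 lost would be a drop-out of only about 23%.

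A third reply is that the loss is small. That is also true. It biases no estimate, leaves the type I error unchanged, and the results will be reported with 95% confidence intervals.

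**Conclusion.** The point holds as an error in the sample-size arithmetic. At the anticipated 30% drop-out, 120 randomised leaves 84 completers against 93 required, so the calculation as stated does not deliver 0.8. That conclusion rests only on the article's own figures.

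The size of the power loss is about 4 to 5 percentage points on a completers basis: 0.81 to 0.76 under the assumed interaction with correlation 0.5, or 0.80 to about 0.75 if 93 gives exactly 0.80. Both pairs are for orientation, because the test and the correlation are assumptions. The power actually achieved could be higher if many drop-outs are not voluntary withdrawals and contribute earlier scores.

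The statement should be corrected. The modest loss does not call the design into question.

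**What to change.** Keep 120 and correct the statement in the Participants section, for example: *With 120 randomised, 93 participants complete only if drop-out is at most 22.5%; at the anticipated 30%, 84 remain.* The sponsor should then give the power at 84 from its own G*Power inputs. The 0.76 above should not be copied in unless those inputs turn out to match the assumed ones. If the sponsor wishes to count on partial data from patients lost for reasons other than withdrawal, it should say so and state how many it expects.

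The cost is one or two sentences and a slightly less favourable stated power. No patients are added and no analysis changes. If the sponsor prefers to hold 0.8 at 30% drop-out, the matching enrolment is 133, or 135 in equal arms, which is 15 more than planned.
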